#### Control group

2.5.2

The primary component of the SYG placebo is dextrin, which was procured by Beijing Tcmages Pharmaceutical Co., Ltd, Batch number: 240601202404121, and the primary component of the NRP placebo is medical starch, which was procured by Liaoning Dongyuan Pharmaceutical Co., Ltd., Batch number: F20190001996. Furthermore, 10% of the raw drug was added to the SYG placebo and NRP placebo to match the odor, color, taste, and texture of the experimental group medication. The packaging, administration, and dosage of the placebo are identical to those of the experimental group. Participants are required to return unused medication and packaging to the investigators after each stage.

#### Removal, dropout, and termination criteria

2.5.3

Participants will be excluded from the study if any of the following conditions are found after the study finishes: a. Participants don't meet the inclusion criteria or meet the exclusion criteria; b. Participants don't adhere to the medication regimen as specified in the study protocol; c. Participants have no post-treatment visit records; d. Participants used concomitant medications during the trial that may affect the evaluation of the efficacy and safety of SYF. Excluded cases should not be included in the efficacy analysis. However, the safety analysis should include those who have received at least one treatment and have at least one safety record.

If participants experience adverse events such as cardiac death, non-fatal myocardial infarction, acute heart failure, severe angina pectoris, severe arrhythmia, or coronary revascularization (PCI or CABG) during the study, or significant deviations occur during the intervention that hinder the evaluation of drug efficacy, participants will be withdrawn from the trial based on the clinical physician's judgment. Participants may voluntarily withdraw from the trial if they are dissatisfied with the efficacy, experience adverse reactions, plan to receive other treatments, or for other reasons leading to unwillingness to continue treatment. Participants who fail to complete the observation period specified in the trial will be considered dropout cases, regardless of the timing or reason. The reasons for dropout will be documented in the case report form (CRF) and included in the final data analysis.

The entire study will be terminated under the following circumstances: a. Occurrence of multiple serious adverse events related to the trial that pose a significant threat to participant safety; b. Quality issues with the investigational drug; c. Unblinding of the entire double-blind trial, or an emergency letter unblinding rate exceeding 20%. The investigator must provide a comprehensive explanation to the ethics committee regarding the reasons for trial termination, submit a written application for termination, and the ethics committee will make the final decision on whether to terminate the trial. If the study is terminated, the investigator shall ensure that participants continue to receive necessary treatment and follow-up after trial termination. Simultaneously, all relevant documents and materials must be properly preserved to assess the trial outcomes and reasons for termination.

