#### Secondary outcomes

2.6.2

The secondary outcome measures of this study include imaging features of plaques, Traditional Chinese Medicine Syndrome Score (TCMSS), the Seattle Angina Questionnaire (SAQ), echocardiography, adverse cardiovascular events, and metabolomic analysis.

The imaging features of plaques include plaque morphology, location, volume, degree of stenosis, and calcification score, all of which will be assessed at baseline and 24 weeks after randomization. Echocardiography and metabolomics analyses will be performed at baseline and 24 weeks after randomization; TCMSS and SAQ will be recorded at baseline and 4th, 12th, 24th weeks after randomization. Adverse cardiovascular events are defined as cardiac death, non-fatal myocardial infarction, coronary revascularization, stroke, severe angina pectoris, and hospitalization due to acute coronary syndrome, malignant arrhythmia, or heart failure occurring within 24 weeks after randomization, and will be recorded at any time following participant enrollment.

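### Cardiovascular events that count as a 24-week secondary outcome are also grounds for withdrawal from the trial, so who is followed, scanned and analysed can depend on the outcome

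*Protocol article*

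**What the plan says.** **Withdrawal (2.5.3).** The triggering events are listed: "If participants experience adverse events such as cardiac death, non-fatal myocardial infarction, acute heart failure, severe angina pectoris, severe arrhythmia, or coronary revascularization". The same sentence adds a second ground and then states the consequence: "PCI or CABG) during the study, or significant deviations occur during the intervention that hinder the evaluation of drug efficacy, participants will be withdrawn". The decision is discretionary, since "participants will be withdrawn from the trial based on the clinical physician's judgment". This is withdrawal from the trial, not only from study drug, and no criterion for the judgment is given. Anyone who does not complete the observation period is a dropout, whatever the reason. The reason is recorded and enters the final analysis.

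**Outcome (2.6.2).** "Adverse cardiovascular events are defined as cardiac death, non-fatal myocardial infarction, coronary revascularization, stroke, severe angina pectoris, and hospitalization due to acute coronary syndrome", and hospitalization for malignant arrhythmia or heart failure is included too. Such events count when "occurring within 24 weeks after randomization, and will be recorded at any time following participant enrollment".

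**Imaging (2.6.1, Table 1).** CT-FFR, WSS and FAI, the primary outcomes, are measured at baseline and week 24 only.

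**Exclusion (2.5.3).** Cases may be excluded for (b) not adhering to the medication regimen, (c) "c. Participants have no post-treatment visit records", or (d) concomitant medication that may affect the evaluation of SYF. For all of them, "Excluded cases should not be included in the efficacy analysis".

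**Analysis sets (2.9).** The FAS holds completers and dropouts that are *analyzable*, a word not defined, and leaves out excluded cases. The PPS, used for sensitivity analysis, requires the full intervention and follow-up.

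**The concern.** Ordinary dropout may or may not be related to outcome. Here the stated rule makes the outcome itself the trigger, and a case-by-case decision settles whether the participant stays. If SYF lowers event rates, more control participants with poor results would be removed and the estimated benefit would shrink. If SYF raises them, the unfavourable difference would shrink in the same way.

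For imaging there is a second problem. CT-FFR is read 2 cm beyond the most severe stenosis, and WSS and FAI are read at it (2.6.4). That lesion is a likely target of revascularization. A participant kept after PCI there contributes a value that reflects the procedure, while one withdrawn contributes none. Which of the two happens is left to judgment.

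**Working it through.** **No figure to reproduce.** The article gives no event rate, dropout rate, SD, effect size or power, and sets 60 participants (30 per group) without a calculation (2.7). The check is mainly textual, and the arithmetic is illustrative.

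**Step 1: overlap of the two lists.**

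| Event | Ground for withdrawal (2.5.3) | Secondary outcome (2.6.2) |
|---|---|---|
| Cardiac death | yes | yes |
| Non-fatal MI | yes | yes |
| Coronary revascularization | yes | yes |
| Severe angina | yes | yes |
| Acute heart failure | yes | if hospitalized |
| Severe arrhythmia | yes | if malignant and hospitalized |
| Stroke | not named (the list is open-ended) | yes |

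**Step 2: what can be lost after an event.**
- The triggering event is recorded.
- Later events before week 24: nothing requires follow-up after withdrawal.
- Week-24 scan: it may be missed, and no other post-baseline scan exists.
- Place in the efficacy set: at risk through (b) if the regimen is broken off, (c) if no visit follows (the first is at week 4), (d) if medication is added because of the event, or through the undefined word analyzable.
- The PPS does not help, since it drops anyone without full follow-up.

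**Step 3: event comparison (assumed 1 SYF and 4 placebo participants with an event).**
- All 60 kept: 1/30 = 3.3% v 4/30 = 13.3% (Fisher p = 0.35).
- Half of the event cases leave the FAS: 0.5/29.5 = 1.7% v 2/28 = 7.1%.
- All leave: 0% v 0%.

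**Step 4: imaging comparison (all inputs assumed).** Let the change be normal with SD 1 and a true difference of 0.50. An event occurs when a latent score with correlation r to the change falls below q, the normal quantile of the control event proportion p. In the SYF group the score is shifted by 0.5r. Deleting event cases raises a group's mean by r·φ(q)/(1−Φ(q)), with q − 0.5r in place of q for SYF. The estimate is 0.50 + rise(SYF) − rise(control).

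| p | r | Rise, control | Rise, SYF | Estimate |
|---|---|---|---|---|
| 13.3% | 0.7 | 0.7 × 0.2152/0.8667 = 0.174 | 0.7 × 0.1372/0.9280 = 0.103 | 0.430 |
| 3.3% | 0.7 | 0.7 × 0.0742/0.9667 = 0.054 | 0.7 × 0.0367/0.9855 = 0.026 | 0.472 |
| 13.3% | 0.3 | 0.3 × 0.2152/0.8667 = 0.074 | 0.3 × 0.1801/0.8963 = 0.060 | 0.486 |

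The loss is about 0.01 to 0.07 SD. A harsher assumption gives more: with 1 v 4 withdrawals and values 1.0 to 1.5 SD worse than the rest, deletion hides (4 − 1)/30 × 1.0 to 1.5 = 0.10 to 0.15 SD. For scale, 30 per arm reaches 80% power only at about 0.72 SD.

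**Step 5: would a worst-rank analysis repair it?** Simulated rank-sum power, 30 per arm, true difference 0.50 SD, 13% control events:

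| r | Deletion | Worst rank |
|---|---|---|
| 0.7 | 36% | 43% |
| 0.3 | about 40% | about 36% |
| 0 | 39% | 27% to 28% |

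Worst rank helps only when events track the imaging change closely or themselves carry the full treatment effect.

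**The case against.** The strongest reply is that the trial does capture these events. They are recorded at any time after enrolment, Table 1 shows continuous monitoring, dropouts can enter the FAS, and dropout reasons are reported. That stands for the triggering event. It does not cover later events or the week-24 scan, and it does not return an excluded case to the efficacy analysis.

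Three stronger readings are tempting, and the documents do not support them.
- *Every event before week 4 is lost.* At a constant hazard, 28/168 = 17% of first events fall before that visit, but this is not a loss rate. It applies only to those who die or are withdrawn, and only if a recorded event contact is not a post-treatment visit record, which the text leaves open. With 4 control events it amounts to at most 4 × 0.167 = 0.7 of an event.
- *Harm would be hidden.* Adverse events, serious adverse events and withdrawals due to adverse events are safety outcomes (2.6.3), and 2.5.3 keeps treated participants with one safety record in the safety analysis. Section 2.9 evaluates safety on the FAS and asks for a safety visit, which does not agree with 2.5.3, but that is a separate inconsistency.
- *The imaging effect is substantially biased.* This needs a high event rate and a strong correlation, and the documents give neither. Participants have CT-FFR above 0.8 and CCS grade I to II angina, so events may be few.

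It is also fair that detailed handling of imaging after an event may sit in an analysis plan not shown here. The withdrawal rule, the exclusions and the FAS definition are fixed in this article, however, and they create the problem. Blinding limits deliberate selection by arm, but not the bias that follows when event rates differ.

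**Conclusion.** The concern holds in a limited form. The stated rules allow participants to leave follow-up, the primary imaging comparison and the efficacy set because of an outcome that the trial means to compare. It is firmest for imaging, which has one post-baseline scan, and narrower for events, where the trigger itself is recorded.

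The size cannot be determined from the documents. In the assumed cases a true 0.50 SD becomes 0.43 to 0.49 SD, and the hidden difference reaches 0.15 SD only under the harsher scenario. With few events in 60 participants the effect is probably small. The point is worth correcting because the correction is cheap, not because a large bias has been shown.

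**What to change.** 1. **Reconcile 2.5.3 with 2.6.2.** State that stopping study drug, which remains a clinical decision, does not end data collection. Event follow-up, and the week-24 scan where feasible, continue to week 24 for anyone still within that window.
2. **Event outcome.** Analyse adverse cardiovascular events in all randomized participants, and do not apply exclusions b to d to this outcome.
3. **Imaging outcomes.** Before unblinding, replace case-by-case judgment with one fixed rule, applied blind, for death, MI or revascularization of the measured vessel. A worst-rank analysis may be added as an optional sensitivity analysis, but should not be the main one, because it loses power when events correlate weakly with the imaging change.

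**Cost.** Wording changes and a few more follow-up contacts. Item 1 has limited reach: section 2.2.1 reports enrolment complete as of July 2025 and the end of the study expected in the first quarter of 2026. Items 2 and 3 need only be settled before unblinding.

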#### Primary outcomes

2.6.1

The primary outcome measures of this study are coronary artery hemodynamic parameters and FAI assessed by CCTA. The coronary artery hemodynamic parameters include CT-FFR and WSS. These parameters will be evaluated at baseline and 24 weeks after randomization.

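### Section 2.5.3 lets participants leave the trial, not only the study medication, after non-fatal events that overlap an outcome, so week-24 primary data can be lost for outcome-related reasons (effect probably modest)

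*Protocol article*

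**What the plan says.** **Withdrawal rule (Section 2.5.3).** The triggers are introduced as examples: "If participants experience adverse events such as cardiac death, non-fatal myocardial infarction, acute heart failure, severe angina pectoris, severe arrhythmia, or coronary revascularization". The same sentence adds significant deviations that hinder the evaluation of efficacy. The consequence is that "participants will be withdrawn from the trial based on the clinical" physician's judgment. The object of withdrawal is the trial, not the study medication.

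**Status afterwards (Section 2.5.3).** "Participants who fail to complete the observation period specified in the trial will be considered dropout cases, regardless of the timing or reason". What is then said to be kept is the reason: "The reasons for dropout will be documented in the case report form (CRF) and included in the final data analysis".

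**Outcome definition (Section 2.6.2).** "Adverse cardiovascular events are defined as cardiac death, non-fatal myocardial infarction, coronary revascularization, stroke, severe angina pectoris, and hospitalization due to acute coronary syndrome"; the list goes on to hospitalization for malignant arrhythmia or heart failure. The window is stated as "occurring within 24 weeks after randomization, and will be recorded at any time following participant enrollment". Table 1 likewise shows continuous event monitoring up to week 24.

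**Primary outcomes (Section 2.6.1 and Table 1).** For CT-FFR, WSS and FAI: "These parameters will be evaluated at baseline and 24 weeks after randomization". No scan is scheduled in between. TCMSS and SAQ are scheduled at baseline and weeks 4, 12 and 24.

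**Analysis set (Section 2.9).** The full analysis set takes completers and those dropouts that can be analysed, and leaves out excluded cases.

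**The concern.** A participant who has one of the listed non-fatal events may stop being observed because of that event. Two consequences follow.

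First, the primary outcomes have a single post-baseline time point. Withdrawal at any time before week 24 leaves no post-baseline CT-FFR, WSS or FAI, and no analysis method can recover a scan that was not done. The participants concerned are those whose disease has declared itself, so the missing values are related to outcome. If such withdrawals differ in number between the arms, the comparison of completers is biased.

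Second, Sections 2.5.3 and 2.6.2 pull in different directions. One allows the participant to leave the trial on having an event; the other records events over the full 24 weeks.

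This is a stated rule of conduct, not a detail left to an analysis plan.

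**Working it through.** **Step 1. Compare the two lists.**

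| Event | Withdrawal trigger (2.5.3) | Outcome component (2.6.2) |
|---|---|---|
| Non-fatal MI | yes | yes |
| Severe angina | yes | yes |
| Revascularization | yes | yes |
| Cardiac death | yes | yes, but no later data can exist |
| Heart failure | if acute | if it leads to hospitalization |
| Arrhythmia | if severe | if malignant and it leads to hospitalization |
| Stroke | not named | yes |
| Hospitalization for acute coronary syndrome | not named | yes |

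The lists overlap but are not the same, although the trigger list is open-ended. The avoidable loss concerns the non-fatal triggers.

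**Step 2. What one withdrawal removes.** All three primary outcomes are lost whenever it happens before week 24. Of the three post-baseline TCMSS and SAQ visits, three are lost if it happens before week 4, two between weeks 4 and 12, and one after week 12. The triggering event is recorded.

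**Step 3. How many participants.** Section 2.7 gives 60 participants, 30 per group, with no sample size calculation. The protocol gives no event or dropout rate, so there is no figure to reproduce and the rates below are assumptions. The expected loss is 60p and the chance of at least one loss is 1 − (1 − p)^60.

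| Assumed share withdrawn for an event, p | Expected loss of 60 | Chance of at least one |
|---|---|---|
| 1% | 0.6 | 45% |
| 3% | 1.8 | 84% |
| 5% | 3 | 95% |
| 10% | 6 | 99.8% |

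**Step 4. Bias of the completers' comparison.** Suppose k_T of 30 on SYF and k_C of 30 on placebo are withdrawn, and their unobserved week-24 values would have been s SD worse than those of completers in the same arm. Dropping them makes each arm look better by (k/30) × s, so the bias in the difference is (k_C − k_T)/30 × s. The values of s are assumed.

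- 1 versus 3 withdrawn: 2/30 × 0.5 = 0.03 SD; 2/30 × 2 = 0.13 SD.
- 2 versus 5 withdrawn: 3/30 × 0.5 = 0.05 SD; 3/30 × 1 = 0.10 SD; 3/30 × 2 = 0.20 SD.
- 2 versus 2 withdrawn with the same s: 0.

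The first split needs 4/60 = 6.7% withdrawn and the second 7/60 = 11.7%. At 3% only about 2 participants leave in total, so an excess of 3 in one arm could not arise.

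For scale, the standard error of a difference between two arms of 30 is √(2/30) = 0.26 SD. A bias of 0.10 SD is about 0.4 standard errors; 0.20 SD is about 0.8.

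The direction depends on which arm loses more. A larger loss on placebo works against SYF; a larger loss on SYF flatters it.

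**Step 5. Precision.** By the normal approximation, with 5% two-sided (sidedness is not stated), 30 per arm detects (1.960 + 0.842) × 0.258 = 0.72 SD with 80% power. With 28, 27 or 25 analysed per arm, power for that difference is 0.772, 0.757 or 0.725.

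**The case against.** The strongest case on the other side has five parts.

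1. **The article may simply not describe follow-up after withdrawal.** Section 2.6.2 and Table 1 can be read as continued event recording to week 24, and the full analysis set admits dropouts that can be analysed. This stands for later events: a reader might infer that only the first event is ever seen, and the text does not establish that. It does not answer the imaging point, because nothing in these passages supplies a week-24 scan for someone withdrawn from the trial.

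2. **Withdrawal is discretionary.** A reader might infer that imaging will be missing in everyone who has an event. The text supports only that it may be missing in some, and deviations count only if they hinder the efficacy evaluation. Blinding also makes it less likely that physicians' judgment differs by arm.

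3. **Later events may not matter.** Section 2.6.2 sets out no recurrent-event analysis. If the outcome is whether a participant had any event, the triggering event already settles it. This stands, and it is why the weight falls on the primary outcomes.

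4. **Not all lost data are recoverable.** Death precludes a scan. Section 2.6.4 takes the primary measures at or just distal to the most severe lesion, so a scan after revascularization of that lesion no longer measures the same thing as baseline. This stands and limits the benefit of the fix.

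5. **Few events are likely.** Section 2.2.3 requires CT-FFR above 0.8 and angina of grade I–II, Section 2.2.4 excludes left main stenosis of 50% or more, follow-up lasts 24 weeks, and Section 2.7 calls the trial exploratory. This makes a modest effect probable. It does not justify giving up data that the schedule already provides for.

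**Conclusion.** The concern holds in a limited form. Section 2.5.3 permits withdrawal from the trial after non-fatal events that overlap a secondary outcome, and after deviations that hinder efficacy evaluation. Because the primary measures have one post-baseline time point, each such withdrawal can remove all of them for an outcome-related reason. The rule is also in tension with the 24-week event window in Section 2.6.2.

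The size is probably modest. The range of 0.03 to 0.2 SD rests on assumed numbers withdrawn and on an assumed shift of 0.5 to 2 SD, none of which the protocol gives. A reader might infer that the primary comparison will be materially biased; the document does not support that, and with balanced withdrawals and the same shift in both arms the bias is zero. The point is still worth acting on: the loss is partly avoidable, and 60 participants leave little room for it.

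**What to change.** Reconcile Sections 2.5.3 and 2.6.2 as follows.

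- Distinguish discontinuation of study medication from withdrawal from the trial. Decisions on study medication stay with the clinician.
- After an event or deviation, unless consent is withdrawn, continue the scheduled event, safety, TCMSS and SAQ follow-up to week 24.
- Obtain the already planned week-24 CCTA where clinically suitable.
- Flag participants whose index lesion was revascularized, since their week-24 lesion measures are not comparable with baseline.
- Report withdrawals by arm and reason.

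If the intention is already to keep following such participants, a clarifying sentence in Section 2.5.3 would settle the first two items.

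The cost is a short amendment that uses visits and a scan already in Table 1, with continued contact with a few participants. Section 2.2.1 reports full enrolment as of July 2025 and expects completion in the first quarter of 2026, so the benefit is limited to participants still in follow-up or retrievable for it. Flagging and reporting can be done for all participants from the records.

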#### Drugs combined and contraindicated in trial

2.5.4

Patients experiencing angina pectoris attacks may take sublingual nitroglycerin or rapid-acting rescue pills. However, the investigator must record the specific date of onset, duration, and relief measures. In addition to the initially administered medications, the investigator shall record all additional drugs and treatments given to the patient in the CRF. During the study period, the use of other traditional Chinese medicine decoctions, intravenous injections, or proprietary Chinese medicines with qi tonification and blood circulation activation effects is prohibited. Acupuncture, cupping, and other appropriate traditional Chinese medicine techniques should not be accepted as treatments.

